### Summary of outcome measure

#### Knowledge

*The Dutch Heart Failure Knowledge Scale (DHFKS)*
[63] is a self-report questionnaire consisting of 15 multiple choice items related to: HF in general (4 items), HF treatment (6 items related to diet, fluid restrictions and activity), symptoms and symptom recognition (5 items). The scale has a minimum score of 0 (no correct answer) and a maximum score of 15 (all answers correct), higher scores indicate better knowledge. The tool developed in the Netherlands and tested on 902 HF patients, was found to be reliable (Cronbach’s α .62) and valid [58]. The scale has been shown to be sensitive in differentiating between patients who had and who had not received education and counselling (*p* < .01) and has been widely used in clinical settings to evaluate patients’ HF knowledge [22, 64, 65].

#### Self-care

*The Self-Care of Heart Failure Index (SCHFI)*
[66] is an instrument that measures HF self-care behaviours and skills through self-report. The SCHFI comprises 15-items with a four-point Likert response scale. It contains three subscales: self-care maintenance, self-care management, and self-care confidence. Self-care maintenance measures symptom monitoring and compliance with HF treatment in order to prevent worsening symptoms such as checking ankles for swelling and eating a low salt diet. Self-care management measures the capability to recognise changes in HF symptoms, assess the meaning of the changes, and make a judgment on appropriate treatment actions. For example, if a patient experiences weight gain of more than 2 kg in two or three days, an appropriate action would be to take an extra diuretic. Self-care confidence measures perceived control to perform self-care in each phase such as how confident they feel in recognising symptom changes when they occur. Scores from each of the three self-care subscales are transformed to 100-point scales; higher scores reflect better self-care. Self-care management scores are only computed for those patients reporting HF symptoms of ankle swelling or trouble breathing in the previous three months [66]. The SCHFI was selected because it is a reliable measure of self-reported self-care skills and behaviours [66] and has been extensively validated among HF populations around the world. The SCHFI has also been reliably translated into Thai [67]. In the Thai context the tool was administered to 400 HF patients and found to be reliable: Cronbach’s alpha coefficient of 0.85 [67].

#### Health-related quality of life

*The Minnesota Living with Heart Failure (MLHF) questionnaire (MLHF)*
[68] is a disease-specific measure of HF HRQoL assessing patients’ perceptions as to the influence of HF on physical, socioeconomic, and psychological aspects of their life. The MLHF consists of 21 questions focused on patients’ perceptions concerning the effects of HF on their physical functioning, such as shortness of breath, fatigue, and peripheral oedema and their emotional life such as memory loss, loss of self-control, and side effects of HF treatment [68]. Patients respond to the 21 items using a 6 -point Likert scale (0 = no; 5 = very much). The total score ranges from 0 to 105; a lower score reflects better HRQoL. Internal consistency reliability of the MLHF using Cronbach’s alpha coefficient was .91 [69]. The Thai version has been used in 422 HF patients, and in pilot testing in a sample of 30, had good reliability with a Cronbach’s alpha coefficient of 0.94 [70].

*The Short-Form 12-item (SF-12) health survey*
[71] is a generic measure of HRQoL that will be used in this study as a combination of generic and disease-specific measures has been recommended. The SF-12 [72] is a shortened version of the original SF-36 [73] and consists of 12 items with a 5-point Likert scale (1 = all of the time, 5 = none of the time). The 12 items include the self-assessment of health, physical functioning, physical role limitation, mental role limitation, social functioning, mental health, and pain. The summary score provides an indication of physical and emotional functioning, with higher scores indicating better HRQoL. The Thai version of the SF-12 has been used with 98 HF patients, reliability in this population was 0.83 [74].

#### Perceived control about managing family member’s heart problems

*The Control Attitudes Scale (CAS)* family version will be used only for the carers of patients with HF in this study [75, 76]. The CAS family version consists of eight items scale with a 5-point response scale (1 = strongly disagree, to 5 = strongly agree). The items address how much perceived control or how helpless individuals feel about managing their family member’s heart problems. Higher scores indicate greater perceived control. Internal reliability of the CAS tested in 21 carers of patients with HF was 0.75.

#### Instrument translation

There are three research tools which will be translated into Thai language: the brief screening questions for detecting in adequate health literacy, the DHFKS, and the CAS. The investigator will use the World Health Organisation [77] model process of translation and adaptation of instruments to guide the questionnaire translation.

#### Data analyses and sample size calculation

Data collected will be entered into the Statistical Package for the Social Sciences (SPSS Inc.). Descriptive statistics will be used to analyse demographic data. The sample size calculation is based on changes in HF knowledge. In a previous study investigating HF knowledge as the primary outcome [22]), a sample size of 50 per group and allowing for a 10% attrition rate, had adequate power (0.80) with a two-sided 95% significance to detect a difference of two-points on the DHFKS between the intervention and control conditions in mean post-test versus pre-test changes on the DHFKS and 93% power to detect clinically significant difference in MLHF scores of 6-points. For this study, assuming a medium effect size (0.65) in the between-group differences on the DHFKS and allowing for a 20% attrition rate, the minimal sample size of 40 per group will have sufficient power (0.80). An independent t-test will be used to test the overall differences of the DFHKS, SCHFI, CAS, MLHF and SF-12 within the groups and between the control group and the intervention group at baseline and over three and six months. Two-way repeated measures analysis of variance (ANOVA) will be used to test the difference between groups and change overtime in each group of the main outcomes (DFHKS, SCHFI, CAS, MLHF and SF-12). Treatment failure and withdrawal will be considered on an intention-to-treat basis, with the aim of providing a more realistic estimate of the difference between the two groups.

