### Recruitment

This trial will enroll a minimum of 100 dyads sourced from two rural hospitals in Thailand. Participants will be identified for enrolment by clinical staff based on inclusion criteria. Potential dyads will be approached at their regular outpatient appointment or contacted via telephone and verbally informed of the study. The dyads who agree to participate will receive a verbal and written explanation of the study by the investigator or the attending nurse, allowing them time to consider and freely participate.

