### Randomisation

The investigator will derive the random allocation from a computer-generated sequence of random numbers. Each dyad will be randomised at a 1:1 ratio in blocks of ten to either the control (usual care) or intervention (family-based education plus usual care) group. The random allocation will be sealed in an envelope and retained by technical staff at each hospital to give to the research assistants. Once participants have consented to the study and baseline data has been collected, the research assistant will open the sealed envelope indicating the group allocation. In this way, the research assistant collecting baseline data will be unaware of which group participants have been allocated to.

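### The sample size section gives 40 per group as already allowing for 20% attrition, but 40 gives 80% power only as the number analysed; the number to randomise is 49 to 50 per group

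*Protocol article*

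**What the plan says.** Under Data analyses and sample size calculation, the protocol article first describes an earlier study with 50 per group and a 10% attrition allowance, which "had adequate power (0.80) with a two-sided 95% significance" for a two-point difference in change on the Dutch Heart Failure Knowledge Scale (DHFKS). It then turns to this trial, "assuming a medium effect size (0.65) in the between-group differences on the DHFKS", and concludes: "allowing for a 20% attrition rate, the minimal sample size of 40 per group will have sufficient power (0.80"). The section does not say whether 40 is the number randomised or the number analysed, and it gives no other group size for this trial.

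The Recruitment section sets the enrolment: "This trial will enroll a minimum of 100 dyads". The Randomisation section fixes equal allocation: "Each dyad will be randomised at a 1:1 ratio in blocks of ten".

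**The concern.** A sample size that allows for attrition is normally the number to enrol, with the loss already built in. The preceding sentence uses the same construction for the earlier study's 50 per group, so a reader will take this trial's 40 in the same way. On that reading 80 dyads would be enough. They would not be: the calculation needs almost 40 per group analysed before any loss.

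What is at stake is the accuracy of the power statement for the patients' primary outcome, HF knowledge. A reader who relies on this section alone would accept a trial of 80 dyads as having 80% power, when after the protocol's own assumed loss it would have about 73%.

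**Working it through.** **Inputs**
- Standardised difference d = 0.65, attrition 20%, power 0.80 and 40 per group: Data analyses and sample size calculation.
- Two-sided 5%: an assumption for this trial. The section states sidedness only for the earlier study, and there it is two-sided.
- 1:1 allocation: Randomisation.
- At least 100 dyads, so at least 50 per group: Recruitment.
- Independent t-test: the first between-group test named in the analysis section.

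**1. The protocol's figure, reproduced as a number analysed**

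Normal approximation: n = 2(z₀.₉₇₅ + z₀.₈₀)² / d² = 2(1.960 + 0.842)² / 0.65² = 2 × 7.849 / 0.4225 = 37.2, so 38 per group. With the noncentral t distribution the solution is 38.14, so 39 per group.

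With 40 analysed per group, power is 0.82 (noncentral t; 0.83 by the normal approximation). The stated 40 and 0.80 therefore reproduce, to within rounding, as a number analysed.

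**2. The same figure read as a number enrolled**

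40 × (1 − 0.20) = 32 per group analysed. Normal approximation: Φ(0.65 × √(32/2) − 1.960) = Φ(0.640) = 0.74. Noncentral t: 0.73. The stated 0.80 does not reproduce.

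**3. The number that does allow for 20% attrition**

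39 / 0.80 = 48.75, so 49 per group (98 dyads). The normal approximation gives 38 / 0.80 = 47.5, so 48 per group (96 dyads). The common slip of multiplying by 1.2 instead of dividing by 0.8 gives 39 × 1.2 = 46.8, so 47. None of these is 40.

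**4. Comparison with the enrolment target**

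100 dyads at 1:1 is 50 per group. 50 × 0.80 = 40 analysed per group, power 0.82. The target also exceeds the 98 dyads found in step 3.

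| Reading of 40 per group | Randomised per group | Analysed per group | Power at d = 0.65 (noncentral t) |
|---|---|---|---|
| Number enrolled, as the sentence reads | 40 | 32 | 0.73 |
| Number analysed, as the Recruitment section implies | 50 | 40 | 0.82 |

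**The case against.** The strongest reply is that the trial itself is sound. The Recruitment section is the only enrolment rule, its floor is 100 dyads, and 100 dyads less 20% is exactly 40 per group. On this view 40 was meant as the number analysed and the sentence is merely loose. That stands as regards the trial's power. It does not rescue the sentence, which gives 40 as the size after allowing for attrition and never mentions 50 per group or 100 dyads.

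A one-sided test would nearly reproduce 40 as a number enrolled: 30 analysed per group, and 30 / 0.80 = 37.5, so 38 enrolled. But the only sidedness the section gives is two-sided.

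A reader might infer several stronger points that the document does not support:

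- *The two sizes conflict, and stopping at 80 dyads would follow the protocol.* They agree once 40 is read as the number analysed, and stopping at 80 would breach the Recruitment minimum.
- *The assumed 0.65 is too large because the earlier study's two points imply less.* If that study's power was exactly 0.80 in a two-sample t-test, two points equal 0.57 to 0.60 standard deviations (50 or 45 analysed per group). If its power was really 0.85 with 45 analysed, the figure is 0.64, close to 0.65. The article gives no standard deviation, does not derive 0.65 from two points, and does not set two points as this trial's target.
- *A baseline-adjusted analysis would secure adequate power for two points.* That needs a correlation between baseline and follow-up, which the article does not give, and a baseline-adjusted model is not among the analyses it names.

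**Conclusion.** The point holds as an error in the stated sample size. With d = 0.65 and a two-sided 5% t-test, 40 per group is right as the number analysed (power 0.82) and wrong as a size that already allows for 20% attrition (power 0.73; 49 per group needed). It would be going too far to conclude that the trial is underpowered at its assumed effect: the minimum of 100 dyads covers the requirement provided that attrition does not exceed the assumed 20%. The conclusion rests on the two-sided 5% level carrying over from the earlier study to this trial. It needs no figure from outside the document.

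**What to change.** In Data analyses and sample size calculation, replace the statement for this trial with wording such as: *50 dyads per group (100 in total) will be randomised so that, after 20% attrition, 40 per group are analysed, giving 82% power for a standardised difference of 0.65 (two-sided 5%).* Delete 40 per group as the minimal sample size allowing for attrition.

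Do not add power figures for a two-point difference or for a baseline-adjusted analysis, since they depend on a standard deviation and a correlation that the article does not give.

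The cost is one rewritten sentence. Enrolment, allocation and analysis are unchanged.

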**Methods:**

This randomised controlled trial will evaluate the effectiveness of an education program on knowledge, self-care and health-related quality of life of Thai HF patients and their carers. Assessments will be conducted at baseline, three and six months. Participants will be assigned by independent random allocation to an intervention (family-based education plus usual care) or a control (usual care) group. Analyses will be conducted on an intention-to-treat basis.

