#### Data collection

Before randomisation all dyads will complete baseline questionnaires. Outcome measures will be collected at three and six months at the outpatient clinic or via telephone interview. Data will be collected by research assistants who are not aware of study group allocation. Questionnaires will take approximately 45 to 60 minutes to complete.

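### An independent t-test is assigned to within-arm change, where the data are paired; the error is conservative and confined to within-arm results

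*Protocol article*

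**What the plan says.** The section on data analyses and sample size calculation names one t-test for two kinds of comparison. The sentence begins "An independent t-test will be used to test the overall differences of the DFHKS, SCHFI, CAS, MLHF and SF-12 within the groups" and continues "and between the control group and the intervention group at baseline and over three and six months". It covers all five instruments, among them both primary outcomes: the DHFKS in patients and the CAS in carers. No paired test is named anywhere in the article.

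The next sentence adds a second analysis of the same five instruments: "Two-way repeated measures analysis of variance (ANOVA) will be used to test the difference between groups and change overtime in each group".

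On the measurement schedule, the abstract says "Assessments will be conducted at baseline, three and six months", and the data collection section says "Before randomisation all dyads will complete baseline questionnaires. Outcome measures will be collected at three and six months". Each participant is therefore their own comparator over time.

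**The concern.** Within one arm, the baseline and follow-up scores come from the same people and will normally be correlated. The independent t-test treats them as two unrelated samples. Its standard error adds the two variances and omits the covariance, so the standard error, confidence interval and p-value for within-arm change do not have their stated properties.

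If the sentence were followed as written, real within-arm changes could be missed on any of the five instruments. An over-wide interval in the control arm could also be misread as showing no change under usual care. In addition, the plan would hold two analyses of the same within-arm change, one of them unsuitable, without saying which governs.

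**Working it through.** **The plan's own figure first.** The sample size rests on the between-arm comparison, "assuming a medium effect size (0.65) in the between-group differences on the DHFKS", with power 0.80. Alpha 0.05 two-sided is stated for the earlier study and is assumed here to carry over.

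- Evaluable per arm = 2 × (1.960 + 0.842)² / 0.65² = 2 × 7.85 / 0.4225 = 37.2, so 38 (39 with the t distribution). The stated 40 per group agrees with this as a number of evaluable dyads.
- 40 / (1 − 0.20) = 50 per arm, or 100 dyads, which is the minimum in the recruitment section.

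None of this depends on the within-arm test.

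**Inputs for the within-arm check.**

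- n = 40 per arm with complete data (50 enrolled less 20% attrition, from the article).
- Between-visit correlation r: not given in the article. Assumed to be 0.3, 0.5 or 0.7.
- Equal SD at both visits and normal scores: assumed.
- Within-arm change of 0.4 SD for the power illustration: assumed.

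**Standard errors, in SD units.**

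- Independent test: √(2/n) = √(2/40) = 0.224.
- Paired test: √(2(1 − r)/n) = 0.187, 0.158 and 0.122 for r = 0.3, 0.5 and 0.7.
- Ratio: 1/√(1 − r) = 1.20, 1.41 and 1.83. The ratio does not depend on n.

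**Type I error and power at n = 40, by simulation.**

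| Assumed r | SE ratio | Type I error, independent | Type I error, paired | Power for 0.4 SD, independent | Power for 0.4 SD, paired |
|---|---|---|---|---|---|
| 0.3 | 1.20 | 2.0% | 5% | 41% | 55% |
| 0.5 | 1.41 | 0.65% | 5% | 39% | 69% |
| 0.7 | 1.83 | 0.07% | 5% | 37% | 89% |

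Simulation is preferable to a normal-tail shortcut here because the SD is estimated. At r = 0.5 the shortcut takes the critical value 1.99 (78 degrees of freedom) times 1.414 = 2.82, which gives 0.5%, somewhat too small.

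**Hand check of one power figure (r = 0.5).** The independent statistic has mean 0.4/0.224 = 1.79 and true spread √(1 − 0.5) = 0.707. Power ≈ P(Z > (1.99 − 1.79)/0.707) = P(Z > 0.28) ≈ 39%.

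**Sensitivity to n at r = 0.5.** With 32 per arm, power is 30% (independent) against 59% (paired). With 50 per arm it is 51% against 80%. At r = 0 the two tests agree.

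**The case against.** The strongest reply is that the very next sentence plans a two-way repeated measures ANOVA for change over time in each group, on the same instruments, and that this analysis respects the pairing. That stands, and it limits the damage considerably. A reader might infer that every within-arm result in the trial would be wrong, but the document supports this only for the t-test output. The ANOVA does not repair the t-test sentence, however: both analyses remain specified for the same change and they can disagree.

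Second, with positive correlation the error is conservative. It gives too few rejections and over-wide intervals, and no excess of false positives. This also stands. A reader might infer that the trial could wrongly declare the education effective, and nothing here supports that.

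Third, the between-arm half of the sentence is a valid use of the test at follow-up, and that is the randomised comparison. This is correct. A reader might also suppose that effectiveness will be judged by significance in one arm and not the other. The article does not say so, and it plans direct between-arm tests.

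Fourth, a journal article condenses, and the wording may be shorthand for independent and paired t-tests. That is possible, but the text does not say it, and someone following the sentence literally would run the wrong procedure.

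The sentence also tests the arms against each other at baseline. Because baseline is collected before randomisation, any difference under proper allocation is due to chance and the test tells the reader little. No planned analysis depends on the result, so this adds nothing to the severity.

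**Conclusion.** The sentence is wrong as written: an independent t-test does not fit repeated measurements on the same participants. Over the assumed correlations of 0.3 to 0.7, the within-arm standard error is 1.2 to 1.8 times too large and the true type I error falls from a nominal 5% to between about 2.0% and 0.07%. The power loss of 69% to 39% holds for an assumed 0.4 SD change at a correlation of 0.5 with 40 per arm. These sizes rest on assumed correlations and equal SDs. The conservative direction needs only a positive correlation, which is usual for repeated scores on one person.

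The fault is confined to within-arm inference. It reaches neither the randomised between-arm comparison at follow-up nor the sample size, and a suitable analysis of change is already planned beside it. The severity is minor to moderate. To read this as a threat to the trial's main conclusion would go beyond the document.

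**What to change.** Rewrite the one sentence so that:

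- the independent t-test is limited to comparisons between the arms at three and six months;
- within-arm change is reported as mean change with a paired 95% confidence interval, from a paired t-test or from the within-subject contrasts of the repeated measures ANOVA already planned;
- claims of effectiveness rest on the between-arm contrast (the group-by-time term), with within-arm change as description.

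Optionally, present baseline values by arm without significance tests.

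The cost is a wording change. Data collection, sample size and the planned ANOVA stay as they are.

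### Neither between-arm analysis is adjusted for baseline, and the ANOVA term that is to be the treatment effect is not fixed

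*Protocol article*

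**What the plan says.** The protocol article's section on data analyses and sample size calculation names two ways of comparing the arms on all five scales.

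- Independent t-tests, among other uses "between the control group and the intervention group at baseline and over three and six months".
- A repeated measures analysis: "Two-way repeated measures analysis of variance (ANOVA) will be used to test the difference between groups and change overtime in each group".

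Neither sentence mentions the baseline score as a covariate. The second names a difference between groups and a change within each group, but no group-by-time term. The Data collection section states: "Before randomisation all dyads will complete baseline questionnaires". The Randomisation section likewise opens the allocation envelope only after baseline data are in.

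The sample size is justified by "assuming a medium effect size (0.65) in the between-group differences on the DHFKS", and the article concludes that "the minimal sample size of 40 per group will have sufficient power (0.80)". The same paragraph says that the calculation is based on changes in knowledge. It does not say whether 0.65 is in units of the follow-up SD or the change-score SD.

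**The concern.** A score taken before randomisation is the most useful covariate that a trial of this kind has. Leaving it out of the comparison gives up precision that has already been paid for, with about 40 evaluable dyads per arm.

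The ANOVA sentence raises a second issue. With three assessments, baseline becomes one level of the time factor. The randomised arms do not truly differ at that visit, so a group main effect averages a zero difference in with the two follow-up differences. Change within each arm is not a randomised comparison. The term that carries a difference in change between arms, group-by-time, is not named. An analyst following the sentence could report quite different quantities as the result, and this affects both primary outcomes (DHFKS in patients, CAS in carers) and the secondary ones.

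**Working it through.** **Inputs from the article.** Effect size d = 0.65; power 0.80; 40 per group; 20% attrition ("allowing for a 20% attrition rate"); recruitment target ("This trial will enroll a minimum of 100 dyads sourced from two rural hospitals in Thailand"); 1:1 allocation; visits at baseline, three and six months.

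**Assumptions.** Two-sided alpha 0.05, which the article states only for the earlier study ("with a two-sided 95% significance to detect a difference of two-points on the DHFKS"). The correlation r between visits is not given; I take it as equal for all pairs of visits and let it run over 0.3, 0.5 and 0.7. The true effect is the same at three and six months.

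**The plan's own figure.** For d = 0.65 and power 0.80, a two-sample comparison needs 38 per arm (normal approximation) or 39 (t-test). Allowing for 20% loss, 39/0.80 = 48.75, so 49 per arm. This fits 100 dyads, with 50 × 0.80 = 40 evaluable per arm. Power of the t-test at 40 per arm is 0.82, so the stated 40 reproduces as the evaluable number. (If 40 were the enrolled number, 32 would remain and power would be 0.73.)

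**ANCOVA at one visit.** Effective size d/√(1 − r²):
- r = 0.3: 0.65/√0.91 = 0.681
- r = 0.5: 0.65/√0.75 = 0.751
- r = 0.7: 0.65/√0.51 = 0.910

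The number per arm for 0.80 power falls from 38 to 34, 28 and 19.

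**ANOVA group main effect, baseline as a level.** Expected estimate (0 + d + d)/3 = 2d/3 = 0.433. The SD of a person's three-visit mean is √((1 + 2r)/3), so the effective size is 0.433/0.730 = 0.593, 0.433/0.816 = 0.531 and 0.433/0.894 = 0.484.

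**ANOVA group-by-time.** Between-arm profile (0, d, d), centred: (−2d/3, d/3, d/3), with sum of squares 2d²/3. Noncentrality (40/2)(2d²/3)/(1 − r) = 5.63/(1 − r) = 8.05, 11.27, 18.78, on 2 and 156 df.

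Power with 40 evaluable per arm, 0.65 in follow-up SD units:

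| r | t-test, one visit | ANCOVA, one visit | Group main effect | Group-by-time |
|---|---|---|---|---|
| 0.3 | 0.82 | 0.85 | 0.75 | 0.71 |
| 0.5 | 0.82 | 0.91 | 0.65 | 0.85 |
| 0.7 | 0.82 | 0.98 | 0.57 | 0.98 |

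A simulation at r = 0.5 (20,000 replicates) gave a mean group-effect estimate of 0.434, with power 0.648 for that term and 0.817 for the six-month t-test.

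The group main effect falls below the t-test in power once (2/3)/√((1 + 2r)/3) < 1, that is, r > 1/6.

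**Sensitivity: 0.65 in change-score SD units.** The follow-up effect is then 0.65 × √(2(1 − r)) = 0.769, 0.650, 0.503. Power of the raw t-test is 0.93, 0.82, 0.60; of ANCOVA 0.95, 0.91, 0.88; of the group main effect 0.87, 0.65, 0.38; of group-by-time 0.85 throughout.

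**The case against.** Several points on the other side are sound.

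- A two-way repeated measures ANOVA also produces the group-by-time interaction, which uses baseline through change and is not diluted. The article neither names nor excludes it, and the sentence can be read as comparing change across arms. A reader might infer that the plan must either ignore baseline or average it into the effect. The text does not support that either/or.
- The article does not call the t-tests raw, and it bases the sample size on changes. Still, the same test is applied at baseline, where no change score exists, so raw scores are the more natural reading.
- A reader might infer that the stated 0.80 power fails. It does not. The article never claims it for an ANOVA group main effect, and the t-test gives 0.82 if 0.65 is in follow-up SD units.
- A reader might also treat chance baseline imbalance as an error in the t-tests. Its standard error is √(2/40) = 0.22 SD, but that is ordinary sampling variation already in the test's standard error. An unadjusted t-test in a randomised trial is unbiased and keeps its type I error. What is lost is precision.
- The gain depends on an assumed r. The article reports Cronbach's alpha of .62 for the DHFKS, which makes 0.7 doubtful for that scale though it is no strict ceiling. At r = 0.3 the gain is about 3 points.

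A condensed article may leave model detail to an analysis plan that is not shown. That weakens any complaint about silence alone. But this article does choose its tests and say what each is for, and that choice can be improved as written.

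**Conclusion.** Two things stand. First, an efficiency loss: no baseline adjustment is named, and ANCOVA has higher power than the single-visit t-test at every correlation examined, by about 3 to 16 points on the follow-up-SD reading. Second, a conditional dilution: if the reported difference between groups is the ANOVA group main effect with baseline as a level, the estimate is two-thirds of the true effect. That fraction does not depend on r, but it does assume an equal effect at three and six months. The accompanying power of 0.75, 0.65 or 0.57 does depend on r.

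The interaction avoids the dilution, but it has lower power than ANCOVA at r = 0.3 and 0.5, and a 2-df test gives no effect size to report. Because the article leaves the term open, the available ANOVA tests run from 0.57 to 0.98 in power over the assumed range of r. None of this makes the planned t-tests invalid.

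**What to change.** State one treatment-effect analysis: a linear or mixed model of the three- and six-month scores, with the baseline score as covariate and arm, visit and arm-by-visit as terms. Report the adjusted between-arm difference with its 95% CI at each follow-up visit. State that neither the group main effect with baseline as an outcome level nor change within an arm will be used as evidence of effect.

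The cost is a change of wording. No new data are needed, and SPSS, already named, fits these models. One scale needs an extra sentence: the article says that SCHFI self-care management is scored only for patients with recent symptoms, so some will have no baseline value on that subscale, and its handling should be stated.
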